## Abstract

**Background::**

Lascufloxacin hydrochloride (LSFX) is a quinolone antibiotic that inhibits DNA gyrase and topoisomerase IV of bacteria, it is anticipated to minimize antibiotic resistance in bacteria. It exhibits antibacterial activity against a relatively wide range of bacterial species, including anaerobic bacteria, and its efficacy and safety against community-acquired pneumonia have been shown; however, its efficacy and safety against nursing and healthcare associated pneumonia (NHCAP) have not been verified.

**Methods/Design::**

Here, a single-arm, open-label, uncontrolled study was conducted in which LSFX was administered to patients with NHCAP at 24 facilities. The research subjects (77 cases) were orally administered 75 mg of LSFX once a day for 7 days. The primary endpoint was the clinical efficacy at the time of test of cure (TOC) (TOC; 5–10 days after the end of LSFX administration), while the secondary endpoints were the efficacy at the time of end of treatment, early clinical efficacy, microbiological efficacy at the time of TOC and end of treatment, and safety evaluation of LSFX.

**Discussion::**

NHCAP is a common pneumonia in clinical settings and a notable pneumonia whose mortality is high compared to community-acquired pneumonia. The present study showed the efficacy and safety of LSFX against NHCAP, which could lead to a larger number of therapeutic options for NHCAP.

## 1. Introduction

Pneumonia is a major infection that was the 4th leading cause of death in Japan in 2011.^[1]^ In Japan, pneumonia is classified into community-acquired pneumonia (CAP), nursing and healthcare associated pneumonia (NHCAP), and hospital-acquired pneumonia based on the site of onset and risk of resistant bacteria. Mortality is different for each type: 6.3%, 15.5%, and 30.4%, respectively, thus, appropriate evaluation and therapeutic options are needed.^[2]^ For CAP and NHCAP, severity is evaluated based on the occurrence of sepsis and with the A-DROP system, and an antibacterial drug is selected for treatment. However, in the case of NHCAP, the risk of resistant bacteria and severity are also considered to select an escalation or de-escalation treatment.

Lascufloxacin hydrochloride (LSFX) is a quinolone antibiotic that exhibits antibacterial activity against a relatively wide range of bacterial species, including anaerobic bacteria, by inhibiting DNA gyrase and topoisomerase IV of bacteria. While the existing quinolone antibiotics strongly inhibit either DNA gyrase or topoisomerase IV, LSFX inhibits both to a similar degree. Thus, it is anticipated to limit antibiotic resistance in bacteria.^[3–6]^

In a Japanese Phase III trial, noninferiority of LSFX against levofloxacin in clinical efficacy at the time of test of cure (TOC) against CAP was verified and its safety was shown to be acceptable; however, there are no data available on the efficacy and safety against NHCAP.^[7]^ Many cases of NHCAP are caused by aspiration and often lead to repetitive pneumonia; thus, LSFX, a drug that is unlikely to lead to resistant bacteria, and could become a useful treatment option.

Presently, we are conducting an open-label, uncontrolled study in which LSFX is administered to patients with NHCAP. The study aims to confirm the rate of cure and adverse events 7 days after the end of treatment (EOT) with LSFX as well as search for the rate of cure and safety profile of LSFX against NHCAP. Herein, we describe the final protocol (version 4.0; April 1, 2022).

## 2. Methods/design

### 2.1. Study design

This clinical trial was designed in accordance with the Standard Protocol Items: Recommendations for Interventional Trials and Consolidated Standards of Reporting Trials 2010 guidelines.^[8,9]^ This is an investigator-initiated, multicenter, open-label, and interventional clinical trial to investigate the efficacy and safety of lascufloxacin for NHCAP.

### 2.3. Participant recruitment

Participants will be recruited from the aforementioned 24 hospitals. All eligible patients will be enrolled according to the inclusion and exclusion criteria. Participants or legally acceptable representatives will be provided with information regarding the study by their respective respiratory specialists and requested to sign an informed consent form if they are willing to participate.

### 2.4. Inclusion criteria

Patients should meet the following criteria to be enrolled:

(1)Patients who are older than 20 at the time of providing informed consent.(2)Patients who present acute manifestation of obvious infiltrates in a chest X-ray or high-resolution computed tomography image obtained within 48 hours of administration of the study drug.(3)Patients who meet both 1) and 2):1)Patients who have at least one of the following symptoms:a.Cough.b.Purulent sputum or sputum with increased purulence.c.Abnormal findings in auscultation or percussion (moist rales, dullness to percussion, decreased breathing sounds, etc).d.Worsening of either or both dyspnea and tachypnea.e.Fever: ≥ 37°C (axillary temperature).
2)Patients who have at least one of the following:a.Increased C-reactive protein (CRP) level.b.Increased white blood cell count (> 10,000/ mm^3^), or stab cells > 15%.c.Hypoxemia (PaO_2_ < 60 Torr or SpO_2_ < 90%).

(4)Patients who are classified as mild or moderate by the A-DROP scoring system.^[12]^(5)Patients who meet at least one of the following:1)Admittance to a long-term care or nursing home.2)Discharge from hospital in the preceding 90 days.3)Elderly or physically disabled people who require care.4)Outpatients who regularly receive infusion therapy (including dialysis, antibiotics, anticancer agents, immunosuppressant drugs, etc.) or hemodialysis.
(6)Patients who are able to take drugs orally.(7)Written informed consent has been provided by the patient or legally acceptable representative to participate in the study.

### 2.5. Exclusion criteria

The exclusion criteria are as follows:

(1)Patients with a previous history of hypersensitivity or serious adverse reaction to quinolones.(2)Patients with complications or a past history of a convulsive disorder, such as epilepsy.(3)Female patients who are pregnant or may be pregnant.(4)Patients with severe dysfunction in the liver or heart.(5)Patients with severe or progressive underlying disease or complication (patients with diabetes with HbA1c > 8.0% regardless of treatment, patients with advanced cancer whose prognosis cannot be expected during the observation period, patients with advanced cancer requiring surgery, etc).(6)White blood cell count ≤ 2000/ mm^3^ at the medical facility.(7)Patients with a severe infection requiring treatment with intravenous antibacterials or mechanical ventilation.(8)Patients with bronchial obstruction or a past history of obstructive pneumonia (but not excluding patients with chronic obstructive pulmonary disease).(9)Patients with primary lung cancer or lung metastasis of a malignant tumor that highly affects the clinical evaluation of pneumonia treatment.(10)Pneumocystis pneumonia (including suspected cases) or active pulmonary tuberculosis (including suspected cases). Patients with eosinophilic pneumonia, interstitial pneumonia, or cystic fibrosis that highly affects the clinical evaluation of pneumonia treatment.(11)Patients who received a systemic antibacterial within 7 days prior to the administration of the study drug (including long-term, low dose macrolide therapy).(12)Respiratory infections caused by pathogens (acid-fast bacilli, fungi, viruses, etc) for which the study drug is not expected to be effective.(13)Patients with active hepatitis B or C virus infection, or HIV infection.(14)Patients who are judged to be unsuitable for participation in this trial by the principal or subinvestigator.

### 2.6. Study protocol

A principal investigator or a subinvestigator of participating medical institutions provides a sufficient explanation to patients or proxies using the consent form and documents approved by the Review Board of Certified Clinical Trials before patients participate in the study. After confirming that the patients or proxies sufficiently understand the details of the study, consent to participate is obtained in writing. The principal investigator or subinvestigator of participating medical institutions confirms that the patients meet all of the inclusion criteria and do not meet any of the exclusion criteria, and input all necessary items into an electronic data capture (EDC) system. When determined to be eligible, an ID code is issued by the EDC system as the case registration number. Patients with NHCAP are orally administered 75 mg of LSFX (Lasvic^®^ tablet) once daily for 7 days. The duration of administration is 7 consecutive days. If the attending physician determines that continued administration is necessary, administration for up to 10 days is possible. Tests and observations are undertaken on day 3 of administration, at the end of treatment, and 1 week after the end of administration (5–10 days) (Table 1).

**Table 1 F1:**
[figure not shown]
Treatment schedule and outcome measures.

In this study, there is no drug or therapy that must be used in combination, but the use of the following drugs during the study period requires caution: formulations that contain aluminum, magnesium, calcium, iron, or zinc; phenylacetic acid- and propionic acid-nonsteroidal antiinflammatory analgesics; rifampicin, phenytoin, or carbamazepine; theophylline or aminophylline hydrate; class IA or III antiarrhythmic drugs; and adrenal corticosteroids (oral agents or injections).

Criteria to discontinue the study are as follows:

•If a patient or their proxy requests to withdraw their consent.•A principal investigator or subinvestigator determines that it is difficult to continue with the study due to illness, etc.•A principal investigator or subinvestigator determines that it is difficult to continue with the study due to adverse events.•If the patient becomes pregnant.•If the patient tests positive for SARS-CoV-2.•A principal investigator or subinvestigator determines that it is difficult to continue with the study for any other reason.

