### 2.7. Adverse events

In the case of adverse events, a principal investigator or subinvestigator of participating medical institutions must promptly take appropriate treatment measures for the patients (including providing an explanation), discontinue or pause the clinical study, and take any other necessary measures. If the adverse events are still present at the time of final observation, the principal investigator or subinvestigator of the participating medical institutions should observe the course until the subjects recover to the state prior to the onset of the adverse events or until they reach a clinically stable state. The principal investigator or subinvestigator should evaluate the adverse events and input them into the EDC system. Severe adverse events are classified into death, illnesses that could lead to death, illnesses that require hospitalization at a medical institution for treatment or extended hospitalization, disabilities, illnesses that could lead to disabilities, or diseases or abnormalities in later generations.

An independent Data and Safety Monitoring Committee will not be established. If participating in this study causes health damage to the patients, the principal investigator or subinvestigator will provide appropriate treatment and other necessary measures. If there is compensation liability for health damages caused by this study, and if patients die or suffer permanent disabilities, said patients will be compensated through clinical research compensation liability insurance.

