#### 2.9.3. Safety endpoints.

All adverse events that occur during the trial will be recorded.

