### 2.12. Statistical analysis

The target population in safety analyses (SAS) was defines as patients registered as study participants and administered the study drug at least once during the study period. The target population of the full analysis set (FAS) was defined as a subset of SAS consist of patients who are able to be evaluated whether “cured” or “not cured” at TOC. The modified FAS was defined as an extension of the FAS that includes patients who are able to be evaluated whether “cured” or “not cured” at the TOC or at the withdrawal from the protocol treatment. The target population in the per protocol set analysis was defined as patients with adherence of equal or higher than 80% to the protocol treatment (doses of the study drug).

The objective of the primary analysis is to obtain the lower limit of the 95% CI of the binomial probability of frequency of “cured.” The Clopper–Pearson method was planned to be used here. The FAS was planned as the target population.

A sensitivity analysis for the primary analysis is planned to evaluate the upward bias in the estimation of the probability of the treatment success, that will be introduced by the exclusion of cases who are withdrawn from the protocol treatment before TOC evaluation, obtained from the primary analysis. Aiming this, the modified FAS was set as the target population of the sensitivity analysis and the 95% CI of the binomial probability was planned to be calculated via the Clopper–Pearson method.

The planned analyses on the secondary endpoints are same with the primary analysis; the 95% CI of the binomial probability but the target population, that was set on the FAS.

Associations of the patients background and the primary/ secondary endpoints were planned to be analyzed exploratorily. The patients background was defined as the results from evaluations on respective patients at the visits for the first administration, or before the date, during the patient’s study period.

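### Stopping for adverse events or illness is worded as leaving the study, so test-of-cure outcomes are lost in early stoppers and new safety events after the stop may be missed

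*Protocol article*

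**What the plan says.** All references are to the protocol article.

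- **Section 2.6, text below Table 1.** A single list is introduced by "Criteria to discontinue the study are as follows". Besides withdrawn consent, pregnancy, a positive SARS-CoV-2 test and a catch-all reason, it contains "A principal investigator or subinvestigator determines that it is difficult to continue with the study due to illness, etc" and "A principal investigator or subinvestigator determines that it is difficult to continue with the study due to adverse events". There is no second list for stopping the drug alone.
- **Section 2.7.** After an adverse event the investigator is to treat the patient and "discontinue or pause the clinical study". A later sentence, beginning "If the adverse events are still present at the time of final observation", requires such events to be followed to recovery or a clinically stable state.
- **Section 2.6, main text.** An assessment is scheduled "1 week after the end of administration (5–10 days"). Section 2.8.3 likewise counts TOC from the last dose.
- **Section 2.9.3.** "All adverse events that occur during the trial will be recorded".
- **Section 2.12.** The safety set holds every registered patient who took at least one dose. The full analysis set (FAS) needs a cured or not-cured rating at TOC; the modified FAS also accepts a rating made at withdrawal from protocol treatment. The sensitivity analysis is justified by an upward bias attributed to "the exclusion of cases who are withdrawn from the protocol treatment before TOC evaluation".

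**The concern.** Of the listed reasons, only withdrawn consent in itself prevents further observation. A patient who stops the drug because of an adverse event, worsening illness or SARS-CoV-2 can still be seen and rated 5 to 10 days later. Wording these reasons as discontinuing the study invites sites to close the record at the stop, and section 2.12 is written as if the TOC evaluation is then absent.

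Two things are at stake. For efficacy, the primary outcome is missing in patients whose reason for stopping is related to how they are doing. For safety, the denominator includes every treated patient, but the observation window may be shorter in those who stopped because they were unwell. Early changes of treatment are foreseen: the Discussion says the design allows a prompt switch after evaluation on Days 3 and 7. With 77 patients at 24 facilities (77 / 24 = 3.2 each), an ambiguous rule may well be read differently from site to site.

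**Working it through.** The plan states no figure on this point, so there is none to reproduce. The check sets the sections against each other and then shows what depends on the answer.

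**1. Is stopping the drug separated from leaving the study?** Sections 2.6 and 2.7 both speak of discontinuing the study. Section 2.12 has a term for leaving protocol treatment, but no section says which assessments continue after that.

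**2. Does an early stopper have a TOC time point?** Yes. Sections 2.6 and 2.8.3 anchor it on the end of administration or the last dose, and neither restricts it to completers.

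**3. Does the analysis plan expect that TOC to be available?** No. Section 2.12 describes patients withdrawn from treatment before TOC as excluded from the primary analysis, and the modified FAS rates them at withdrawal. Points 2 and 3 do not fit together: either these patients attend TOC and can enter the FAS, or the visit is not kept for them.

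**4. What safety information is secured after an early stop?**
- Event still present at final observation: followed under section 2.7.
- New event or death with no adverse event open at the stop: no explicit rule. Section 2.9.3 covers the trial period, but its end is not defined for someone who has discontinued the study.
- Denominator: unchanged, since the safety set needs only one dose.

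**5. Window per patient** (7-day course, up to 10 days; TOC 5 to 10 days after the last dose):
- Completer: 7 + 5 = Day 12 to 7 + 10 = Day 17; after a 10-day course, up to 10 + 10 = Day 20.
- Stop on Day 3, visit kept: 3 + 5 = Day 8 to 3 + 10 = Day 13.
- Stop on Day 3, observation ended at the stop: Day 3. The 5 to 10 days after the last dose are lost.

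**6. Illustration only.** The documents give no discontinuation rate. Assume that a share d = 5% to 30% of 77 patients (0.05 × 77 = 3.9 to 0.30 × 77 = 23.1) stops on day s = 3 or 7, that all observation then ends, and that the planned window is T = 12 to 17 days. The share of planned safety person-days lost is d × (T − s) / T.

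| d | Smallest (s = 7, T = 12) | Largest (s = 3, T = 17) |
|---|---|---|
| 5% | 0.05 × 5/12 = 2.1% | 0.05 × 14/17 = 4.1% |
| 10% | 4.2% | 8.2% |
| 20% | 8.3% | 16.5% |
| 30% | 12.5% | 0.30 × 14/17 = 24.7% |

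For any given d these are upper bounds, because section 2.7 keeps patients with an open adverse event under observation. They are measured against a completer's calendar window. Keeping TOC at 5 to 10 days after the actual last dose would recover 5 to 10 of the 12 − 3 = 9 to 17 − 3 = 14 days that a Day 3 stopper would otherwise lack. Each patient with a missed event would lower a proportion based on 77 by 1/77 = 1.3 percentage points.

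**The case against.** The strongest reply is that nothing in the article says safety collection ends at discontinuation. Section 2.12 defines efficacy sets, and its wording on treatment withdrawal differs from that of the discontinuation list in section 2.6. The post-treatment visit is tied to the last dose, so it already fits early stoppers. The safety set keeps everyone. A patient stopped for an adverse event would normally still have it, so that event, and a death arising from it, falls under the follow-up in section 2.7. Table 1 is not visible and the article condenses a fuller protocol, either of which may contain a discontinuation visit. The efficacy bias is already acknowledged and has a sensitivity analysis.

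Much of this stands. A reader might infer that early stoppers certainly leave before safety follow-up and that adverse events and deaths are under-counted as a matter of fact; the documents do not support that. Nor do they support a count of missed deaths. The 15.5% mortality in the Introduction is for this type of pneumonia in general, whereas the trial enrols mild and moderate cases and excludes those needing intravenous antibacterials or ventilation; without a discontinuation rate it cannot be turned into missed deaths. A reader might also see a defect in pregnancy ending participation while abnormalities in later generations count as serious. That item is a seriousness category, not an endpoint, and women who are or may be pregnant are excluded.

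What the reply does not remove is the mismatch between the visit anchor in sections 2.6 and 2.8.3 and the treatment of withdrawn patients in section 2.12. The modified FAS does not repair it: a rating at withdrawal is made at a different time from TOC and cannot show what happened afterwards.

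**Conclusion.** The point holds in a limited form. The stated rules, not merely a gap in an abridged text, word stopping for adverse events, illness or SARS-CoV-2 as discontinuing the study and treat treatment withdrawal before TOC as loss of the TOC evaluation. TOC outcomes are therefore lost in patients who stop early, and section 2.12 itself gives the direction of the resulting bias in the cure proportion as upward.

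The safety consequence is a risk, not an established under-count. It is confined to new-onset events and to deaths that do not arise from an adverse event already being followed.

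The documents give no basis for sizing either loss. The 2% to 25% of safety person-days shown above follows from assumed discontinuation shares of 5% to 30% and from assuming that observation ends at the stop. The conclusion rests on the text shown; a discontinuation visit in Table 1 or the full protocol would reduce the safety risk, but section 2.12 would still need to be reconciled with it.

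**What to change.** Reconcile sections 2.6, 2.7, 2.8.3, 2.9.3 and 2.12:

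- Separate discontinuation of study drug from withdrawal from the study, reserving the latter for patients who withdraw consent to follow-up.
- For every treated patient who has not withdrawn that consent, keep the TOC assessment 5 to 10 days after the actual last dose, and collect new adverse events and vital status to that point.
- State that window in section 2.9.3, and keep the existing follow-up of unresolved events in section 2.7.
- In section 2.12, use the TOC rating of early stoppers where it can be made, and keep the rating at withdrawal for the sensitivity analysis. Some of these patients may still be indeterminable under section 2.8.3, so the change reduces the missing outcomes but does not abolish them.

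No rule on when treatment is stopped needs to change. The cost is amendment wording plus a few retained visits or contacts for patients who stop early; no new visit type is needed.

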### 2.7. Adverse events

In the case of adverse events, a principal investigator or subinvestigator of participating medical institutions must promptly take appropriate treatment measures for the patients (including providing an explanation), discontinue or pause the clinical study, and take any other necessary measures. If the adverse events are still present at the time of final observation, the principal investigator or subinvestigator of the participating medical institutions should observe the course until the subjects recover to the state prior to the onset of the adverse events or until they reach a clinically stable state. The principal investigator or subinvestigator should evaluate the adverse events and input them into the EDC system. Severe adverse events are classified into death, illnesses that could lead to death, illnesses that require hospitalization at a medical institution for treatment or extended hospitalization, disabilities, illnesses that could lead to disabilities, or diseases or abnormalities in later generations.

An independent Data and Safety Monitoring Committee will not be established. If participating in this study causes health damage to the patients, the principal investigator or subinvestigator will provide appropriate treatment and other necessary measures. If there is compensation liability for health damages caused by this study, and if patients die or suffer permanent disabilities, said patients will be compensated through clinical research compensation liability insurance.

